## RESEARCH APPROACH

### B. Research methodology

**Study Location:** The study will be conducted in Hospital Sungai Buloh, Selangor, Malaysia.

**Study Design:** It will be an experimental (randomized Controlled Trial) study design, single-blinded among newly diagnosed HIV positive patients who are eligible to commence ART from December 2013 to August 2014. Following enrollment and allocation to study arm, baseline adherence, clinical symptoms, CD4 count, viral load, Weight, TB status and Opportunistic infection index will be assessed and measured for the 2 groups, prior to the commencement of ART. The intervention group will receive appointment and medication reminders by text-messaging and telephone calls, in addition to standard care. Based on the Theory of Planned Behaviour Model (Ajzen, 1985), appointment reminders will be sent by Short Text Message (in Malay and English languages) three days prior to each individual client's scheduled appointment and telephone call reminders a day prior to the scheduled clinic appointment visits. Weekly short text messages will also be sent to clients to remind them of taking their medications. The control group will only receive standard care and paper-based appointment during clinic visits. Both groups of clients will be followed up for a period of 6 months on ART. Repeated CD4 count, viral load, Weight, TB status and OI index assessment and measurements will be conducted at 3 and 6 months, respectively to determine treatment outcome. Medication adherence will be measured using structured self-report questionnaires. Clinic visits will be measured through medical records of clinic attendance and clinicians' notes.

**Study Duration:** Recruitment and data collection will be from December 2013 to February 2015.

**Study population:** The study population is all HIV positive clients assessed and found to be eligible for ART commencement at Hospital Sungai Buloh, Selangor

**Inclusion criteria:** Age range of 15 to 65 years eligible to commence ART, able to read text messages and have a mobile phone access.

**Exclusion criteria:** Clients who are previously or currently on ART, foreigners & pregnant patients

**Sampling frame:** It is the list of all HIV positive clients assessed and found to be eligible for ART from December 2013 to August 2014 in Hospital Sungai Buloh, Selangor

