
**Data collection:** Research data will be collected using the below plan:

- **How:** 2 types (Primary and Secondary) of data will be collected from 3 main sources;

(a) Hospital medical records – Patients’ socio-demographic and clinic attendance data will be collected from hospital records; pharmacy records will be utilized for measuring adherence to drug refill appointments, while clinicians’ notes will be assessed for clinical information regarding weight, TB status, and OI index of clients (through standardized OI monitoring forms). Laboratory records will be accessed for baseline and follow-up CD4 count and viral load test results.

(b) Structured questionnaire and standardized medication adherence monitoring forms would be used to collect information from clients’ medication adherence self-reports during interaction with clinician/nurses/pharmacists at every scheduled clinic visit/appointment.

- **Who and When:** Socio-demographic (at enrolment) and clinic visit information (at every visit) will be collected by clinic medical record officers, laboratory information by laboratory scientists (at baseline, Months 3 and 6) and clinical and medication adherence information will be collected by clinicians/nurses/pharmacists at every client visit.

A log book on phone calls and text messages will also be recorded.

- **Duration:** Data will be collected over a 13 months period.
- **Questionnaire:** The Adult AIDS Clinical Trial Group (AACTG) adherence questionnaires (Chesney, M.A. et al, 2000) will be adapted with slight modifications, for the purpose of this study. Specialized questionnaires will be used at baseline and follow up. The questionnaire will be pre-tested on a population not included in the sample for validity and reliability.

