The second primary outcome is (regularity of) scheduled clinic attendance at six months. This will be assessed from records of scheduled clinic visits in the medical records unit and supported by record of scheduled drug pick-up in the pharmacy. Regularity of scheduled clinic visits will be calculated based on number of scheduled clinic visits attended and/or number of times defaulted. Number of missed appointments will be analyzed as a continuous variable and polytomous variable. Subjects will be considered as "Regular clinic attendee" if they never missed any scheduled clinic appointment. A "Defaulter" will be a patient who has missed one or more scheduled clinic appointment for any reason(s), while a patient will be considered "Lost-to-follow-up" if s/he refuses to show up for scheduled clinic visit for 3 consecutive months, after 3 consecutive attempts to track the client and bring them back on treatment. The six month scheduled follow-up is the primary analysis but the three month assessment will allow for evaluating trends.

**Secondary Outcomes:** The first secondary outcome is (improved) clinical status of patients at six months. This will be assessed by measuring their weights, assessing their TB and opportunistic infection status at every clinic visits, particularly at three and six months and comparing these with the baseline status. Patients' weight is routinely measured and recorded by nurses at the study site, as part of standard patient management protocol. These records will be accessed and utilized in the analysis. Patients' TB status is also routinely assessed and recorded by clinicians/nurses/adherence counselors at every clinic visits. These records will be accessed and utilized to categorize patients into four groups, namely "No signs and symptoms of TB", "TB suspected and referred for evaluation", "Currently on INH prophylaxis" and "Currently on TB treatment". Opportunistic infection status will be assessed through WHO clinical staging at every clinic visits. The six month scheduled follow-up is the primary analysis but trend will be evaluated at three months.

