The other secondary outcome is (improved) immunologic status/response of patients at six months. This will be assessed based on records of two (2) laboratory measurements – CD4 T cell count and viral load. Patients' CD4 count results at six months will be assessed and compared with baseline values to determine if there's a consistent increase (or otherwise) as expected with strict medication adherence. If patients are adherent to ART regimens, absorb the drugs normally, and if their virus is not resistant to the ART drugs in the regimen, it is expected that their CD4 count should increase from baseline levels by at least 50 cells per microliter of blood within 6-12 months of initiating treatment. CD4 count value at six month scheduled follow-up is the primary analysis.

Similarly, plasma HIV RNA load results at six months will be assessed and compared with baseline levels to determine if there is a significant suppression at six months. If patients are adherent to ART regimens, absorb the drugs normally, and if their virus is not resistant to the ART drugs in the regimen, it is expected that their plasma HIV load should be suppressed to undetectable levels (<400 copies/ml) by six months and remain suppressed thereafter. Analysis of "suppressed" (<400 copies/ml) versus "failure to suppress" (>400 copies/ml) at six months as a dichotomous variable is the primary analysis.

**Data analysis:** Data collected will be collated, checked, cleaned, entered into and analyzed using Statistical Package for Social Sciences software (SPSS) version 21 and AMOS software. Parametric tests (T-test, repeated measures ANOVA) and non-parametric tests will be conducted on the data. P value for test of significance of results will be set at 0.05, alpha level (Type 1 error) at 0.05 (Confidence Interval of 95%), Power at 80% to detect an impact of 15% in the fraction of patients with adherence of at least 90% (assuming a no intervention median adherence level of 90%) using a two-tailed test, Z=1.96, and strength by effect size analysis. Analysis will be by intention-to-treat and complete case analysis.

| Independent variable                                                    | Dependent variable                                                           | Type of analysis                                                           |

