|-------------------------------------------------------------------------|------------------------------------------------------------------------------|----------------------------------------------------------------------------|
| Categorical (socio-demographic, behavioural & adherence factors) | Continuous (Wt, CD4, viral load)                                      | T-test, Repeated Measures ANOVA                                     |
| Categorical & Continuous (All IVs)                           | Categorical (adherence level, TB status, OI index, viral suppression) | Multivariate/Multinomial Logistic Regression Model                  |
| Categorical (All IVs converted to categorical)                   | Categorical (All DVs converted to categorical)                        | -Structural Equation Modelling
-Chi-square (sub-group analysis) |

**Limitations:** (1) Self-report of adherence – exaggeration of true adherence (Pharmacy refill records, CD4 count and viral load will provide a means of validating the responses)

(2) Pill count will not be used

(3) Structured questionnaires may not elicit in-depth information

**Ethical considerations:** The study and materials will be presented to the UPM Ethics approval committee and the Malaysian Ministry of Health's Institutional Review and Ethics Committee for review and approval. Thereafter, permission will be sought from the Medical Director of the hospital in writing to use their clients. The researcher will work in collaboration with attending clinicians, nurses and pharmacists in identification and monitoring of the clients.

**Expected outcomes:** The expected outcomes of this research include:

1. A significant difference in treatment adherence (medication adherence and regular, scheduled clinic attendance) is expected in the intervention group compared to the control group.
2. Better clinical outcome in the intervention group compared to the control group.
3. Socio-demographic, psychosocial and other risk factors that determine differences in treatment adherence between the intervention and control groups will be identified.
4. Provide baseline information on the effectiveness of current standard of care (routine adherence counselling) on treatment adherence and clinical outcomes.

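### Repeated measures ANOVA, if fitted to baseline, month 3 and month 6, drops patients with an observed month-6 weight (and CD4, if measured at month 3) who missed the month-3 visit

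*Protocol*

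**What the plan says.** All places are in the Protocol, section B, Research methodology.

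- **Method.** The Data analysis text says "Parametric tests (T-test, repeated measures ANOVA) and non-parametric tests will be conducted on the data". Row 1 of the table below it assigns "T-test, Repeated Measures ANOVA" to the continuous outcomes weight, CD4 and viral load. The independent variables in that row are "socio-demographic, behavioural & adherence factors"; study arm is not named.
- **Analysis set.** "Analysis will be by intention-to-treat and complete case analysis". The protocol does not say what happens to a patient who misses an intermediate visit.
- **Time points.** Study Design says "Repeated CD4 count, viral load, Weight, TB status and OI index assessment and measurements will be conducted at 3 and 6 months", after a baseline assessment. Data collection has "laboratory information by laboratory scientists (at baseline, Months 3 and 6". The information table under Data collection, however, gives CD4 and viral load at baseline and 6 months only. Weight is recorded at every visit, with months 3 and 6 singled out.
- **Primary time point.** For clinical status, which includes weight: "The six month scheduled follow-up is the primary analysis but trend will be evaluated at three months". For CD4, the month-6 value is also named as the primary analysis.
- **Attendance.** Regularity of scheduled clinic attendance is the second primary outcome, and one missed appointment makes a patient a defaulter.

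**The concern.** Classical repeated measures ANOVA needs a value at every time point in the model. With baseline, month 3 and month 6 entered, a patient weighed at baseline and month 6 but absent at month 3 contributes nothing. Month 3 is there only to show the trend, yet it would decide who counts in the comparison.

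The missing visits are unlikely to be a random sample. Missing a visit bears on the second primary outcome and is what the reminders are meant to prevent. If the reminders work, fewer patients are dropped from the intervention arm than from the control arm. If those dropped are mostly the poorer adherers, the retained groups look more alike than the randomised groups. The effect on weight or CD4 would then be understated, and observed month-6 values would be lost as well.

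**Working it through.** **1. The plan's own figure.** Inputs from Sample size: SD 132, difference 550 - 500 = 50, Z values 1.96 and 0.842.

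n = 2 x 132² x (1.96 + 0.842)² / 50² = 34,848 x 7.851 / 2,500 = 109.4, so 110 per group. Adding 10% gives 121, and two groups give 242. The stated figures reproduce, provided the difference is squared. The formula as printed divides by 50 and would give about 5,472.

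**2. Does the deletion occur?** It depends on which time points are measured and entered.

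| Outcome | Month 3 measured? | Patient with month 6 but no month 3 |
|---|---|---|
| Weight | Yes, consistently | Dropped if all three points are entered |
| CD4, viral load | Yes in Study Design and in the Data collection text; no in the information table | Dropped only if month 3 is measured and entered |

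As a check, a standard repeated measures ANOVA routine was given three time points with one value removed. It refused the data as unbalanced.

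**3. Possible bias, in CD4 cells.** The protocol gives no inputs for weight, so this illustration uses CD4 and applies only if month-3 CD4 exists.

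- From the protocol: a gain of 50 cells in adherent patients; an impact of 15% on the fraction with adherence of at least 90%, read as 15 points.
- Inferred: a no-intervention median adherence of 90% puts about 50% of controls at or above that level, hence about 50% v 65%.
- Assumed: no gain in non-adherent patients; month 3 alone missed by m = 20-50% of non-adherent and k = 0-5% of adherent patients.

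True difference = 50 x 0.15 = 7.5 cells. The adherent share among retained patients in an arm with adherent share a is

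a(1 - k) / [a(1 - k) + (1 - a)(1 - m)].

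| m | k | Control share | Intervention share | Retained difference (cells) | Loss |
|---|---|---|---|---|---|
| 0.20 | 0.05 | 0.543 | 0.688 | 7.26 | 3% |
| 0.20 | 0 | 0.556 | 0.699 | 7.17 | 4% |
| 0.50 | 0.05 | 0.655 | 0.779 | 6.20 | 17% |
| 0.50 | 0 | 0.667 | 0.788 | 6.06 | 19% |

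The loss is 0.24 to 1.44 cells. With 109 per arm after 10% attrition, the standard error of the arm difference is 132 x √(2/109) = 17.9 cells. The largest loss is therefore 1.44 / 17.9 = 0.08 standard errors.

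**4. Possible loss of power.** Two-sample normal approximation, difference 50, SD 132, power = Φ(50 / [132√(2/n)] - 1.96):

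| Loss at month 6 | Further loss for missing month 3 (assumed) | n per arm | Power |
|---|---|---|---|
| 10% | 0% | 108.9 | 79.8% |
| 10% | 5% | 103.5 | 77.8% |
| 10% | 10% | 98.0 | 75.5% |
| 10% | 20% | 87.1 | 70.5% |

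This is the power of the month-6 comparison used for the sample size, not of the ANOVA itself. Steps 3 and 4 rest on different true differences (7.5 and 50 cells) and should not be combined. At 7.5 cells, power is about 7% even with 109 per arm.

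**The case against.** Four stronger readings are tempting, and the document supports none of them.

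- **The plan discards these patients for both weight and CD4.** It lists a T-test beside the ANOVA and names month 6 as primary. A month-6 T-test keeps every observed month-6 value. The protocol does not say which time points enter the ANOVA or which method gives the main result. For CD4, under the information table's schedule, there is no month-3 value to miss. Deletion follows from one of two listed methods; it is not a stated rule.
- **Row 1 prescribes a biased arm comparison.** The row does not name study arm. Its use for that comparison is inferred from the general sentence on parametric tests, from hypothesis H2, and from the absence of any other row for continuous outcomes.
- **The method breaks intention-to-treat.** Complete case analysis is openly declared beside intention-to-treat, and the handling of missing values may be set out in a statistical analysis plan that is not shown. A defaulter may also attend late and still have a value near month 3.
- **The effect is understated by 11-40%.** That follows from the same formula with 75% v 90% adherent (6.68 to 4.51 cells out of 7.5). That split is not the plan's: a median of 90% implies about 50% v 65%.

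It is also fair to say that these are secondary outcomes and that neither primary outcome is in row 1. CD4 is nevertheless the basis of the sample size. What remains is that a named method can drop patients with observed primary-time-point data, for a reason tied to the intervention, and nothing in the protocol prevents it.

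**Conclusion.** The point holds in conditional form. If baseline, month 3 and month 6 are entered, repeated measures ANOVA drops patients with an observed month-6 value who missed month 3. This applies to weight. It applies to CD4 only once the schedule is reconciled in favour of a month-3 measurement. Because attendance is a primary outcome and the target of the reminders, the retained set is selected after randomisation. The likely direction is toward no effect, on the assumption that those who miss month 3 are mainly the poorer adherers.

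The size cannot be found from the document, which gives no month-3 miss rate. In the illustration the bias is about 3-19% of a 7.5-cell difference, at most about 1.4 cells, which is small against a standard error of about 18 cells. Only the 50 cells and the 15 points come from the protocol; 50% v 65% is inferred from its median, and the rest is assumed. A further 10% deletion, also assumed, takes power for a 50-cell difference from about 80% to about 75%. The case for change rests on avoiding a needless selection at almost no cost, not on a large demonstrated bias.

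**What to change.** - In row 1 of the Data analysis table, replace the repeated measures ANOVA with a linear mixed model for repeated measures, with arm, visit, arm-by-visit interaction and baseline value. Fit it to all randomised patients with at least one post-baseline value. Name study arm as the independent variable.
- State that the month-6 arm contrast is the reported result and that month 3 describes the trend.
- Reconcile the CD4 and viral load schedule: Study Design and the Data collection text give months 3 and 6, the information table gives month 6 only. If CD4 is measured only at baseline and month 6, use a baseline-adjusted month-6 comparison (ANCOVA) instead.

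Every observed month-6 value then counts, whether or not month 3 was attended. The model still assumes that missing values are explained by the observed data, and it does not recover patients with no post-baseline value. The cost is a line or two in the protocol and slightly more analysis work. The named software, "Statistical Package for Social Sciences software (SPSS) version 21 and AMOS software", can fit the model through SPSS. No new data, visits or patients are needed.

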**Sampling unit:** Individual patients who are HIV positive but ARV-naïve, assessed and found to be eligible to commence ART based on CD4 < 500 cells/ml and/or WHO stage 3 & 4 disease.

**Sampling method:** A simple random sampling method will be used to select eligible patients for the study.

**Random allocation:** Participants will be allocated to either of the intervention or control groups based on simple, complete randomization technique using their unique ID numbers from a random number table. An independent project biostatistician will generate 1:1 randomization numbers for study arm assignments using a random number generating program. Random allocation will consider and eliminate all forms of possible bias based on the socio-demographic characteristics of the clients.

**Allocation concealment:** Written allocation of assignment will be sealed in individual opaque envelopes marked with study identification numbers which will be available in the study clinic to allocate the target number of participants. After consenting to participate and meeting the inclusion criteria, screened subjects will be enrolled and immediately afterwards are assigned to a randomized study arm by the study coordinator opening the sealed envelopes to determine allocation. Age and gender will be assessed for balance of study arm allocation.

**Blinding:** Investigators will be blinded to intervention assignments.

**Sample size:** The formula for hypothesis testing was used (Lameshow et al., 1990).

$$n = 2d^2[Z_{1-\alpha/2} + Z_{1-\beta}]^2 \mu_1 - \mu_2$$

Where: d = estimated standard deviation (assumed to be equal for each group) is 132 cells/ $\mu$ l (Ref: 10, Table 1)

$\mu_1$  = estimated mean CD4 count increase after commencement of ART with >90% adherence is at least 50cells/ $\mu$ l (14.3%) i.e 550 $\pm$ 50

$\mu_2$  = estimated mean baseline CD4 count at commencement of ART (Based on WHO 2013 guideline of when to commence ART, which is CD4 = 500 cells/ml of blood)

$Z_{1-\alpha/2}$  = standard error when  $\alpha = 0.05$  (95% Confidence Interval) = 1.96

$Z_{1-\beta}$  = standard error associated with power = 0.842 ( $\beta = 0.20$ ) Power ( $1-\beta$ ) = 80%

Expected CD4 increase within 6 months of treatment with >95% adherence is 50 cells/ml

$n = 2 \times (132)^2 [1.96 + 0.842]^2 / (550 - 500)$

$n = 110$  which is the minimum required sample size  $110 + 10\%$  of  $110 = 121$  (attrition)

$121 \times 2 = 242$  (for experimental and control groups)

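### Expected outcome 3 is a question of effect modification, but the only method labelled for subgroups is a chi-square, which does not test it under either reading, and no arm-by-factor interaction is named

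*Protocol*

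**What the plan says.** All places are in the Protocol, section B, Research methodology, unless stated otherwise.

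- **Expected outcomes, item 3:** "Socio-demographic, psychosocial and other risk factors that determine differences in treatment adherence between the intervention and control groups will be identified".
- **Data analysis table, third row** (independent and dependent variables all made categorical): structural equation modelling and "Chi-square (sub-group analysis)". The row does not say which groups are compared, which subgroups are meant, or how a factor comes to count as identified.
- **Data analysis table, second row** (adherence level among the outcomes, all independent variables as predictors): "Multivariate/Multinomial Logistic Regression Model". No interaction term is mentioned.
- **Data analysis text:** "P value for test of significance of results will be set at 0.05", "using a two-tailed test, Z=1.96". The adherence effect is given as "Power at 80% to detect an impact of 15% in the fraction of patients with adherence of at least 90" percent, "assuming a no intervention median adherence level of 90" percent.
- **Objectives, item 1, and hypothesis H1 (Introduction):** these concern socio-demographic factors related to adherence in patients generally. They do not concern factors that change the effect of the reminders.

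**The concern.** Item 3 has a specific null hypothesis: the arm difference in adherence is the same at every level of the factor. A test fits only if it can reject that null.

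The sub-group chi-square can be read in two ways:

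- **Arm by adherence, within each level of a factor.** The null is that there is no arm effect in that level. Two such tests can disagree although the effect is identical in both levels, because each has low power.
- **Factor by adherence.** The null is that the factor is unrelated to adherence. This suits objective 1 and H1, but says nothing about whether the reminders work better in one group than in another.

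Under either reading, the named method and the stated aim do not match. At stake is a report that reminders work only in some patients when the data show nothing of the kind. The Introduction (Significance of research) says that the results are meant to inform policy decisions on service delivery and scale-up.

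**Working it through.** **1. The plan's own sample size.** Inputs from Sample size: "estimated standard deviation (assumed to be equal for each group) is 132 cells"/µl, difference 50, Z values 1.96 and 0.842.

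2 × 132² × (1.96 + 0.842)² / 50² = 109.4, so 110 per arm. The printed formula omits the square on the difference, but the stated result needs it. 110 × 1.10 = 121 per arm, 242 in all. This size comes from CD4 count, not from adherence.

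**2. The planned adherence effect.** A control median of 90% puts about half of the controls at or above 90% adherence. The 15-point impact is therefore taken as 50% v 65%. At 110 to 121 per arm, the power of the whole trial for this effect is 62% to 66%.

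**3. Power inside one subgroup.** Assume a two-level factor split 50/50 and the same true effect in both levels. With n per arm in the subgroup, p0 = 0.50, p1 = 0.65 and mean p = 0.575:

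power = Φ{ [0.15√n − 1.96√(2 × 0.575 × 0.425)] / √(0.50 × 0.50 + 0.65 × 0.35) }

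- n = 55 (110 per arm): Φ{(1.112 − 1.370)/0.691} = 35.5%
- n = 60.5 (121 per arm): Φ{(1.167 − 1.370)/0.691} = 38.4%

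**4. Chance that exactly one of the two subgroups is significant.** The subgroups are independent, so with powers a and b this is a(1 − b) + b(1 − a).

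- 110 per arm: 2 × 0.355 × 0.645 = 45.8%
- 121 per arm: 2 × 0.384 × 0.616 = 47.3%

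The same formula for other splits, with simulation (uncorrected chi-square) alongside:

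| Split | Formula, 110 to 121 per arm | Simulation, 110 to 121 per arm |
|---|---|---|
| 50/50 | 46% to 47% | 45% to 48% |
| 70/30 | 48% to 50% | 49% to 51% |
| 80/20 | 51% to 54% | 53% to 54% |
| 90/10 | 56% to 59% | 56% to 58% |

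**5. Comparator.** On the same simulated data, an arm-by-factor interaction test on the logit scale rejects in 4.8% of trials at 50/50 and 3.6% at 90/10 (110 per arm).

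**6. Sensitivity.**

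- *Size of the common effect* (control 50%, split 50/50, formula and simulation together): 9% to 11% at 0 points, 14% to 15% at 5, 30% to 31% at 10, 46% to 48% at 15, 47% to 49% at 20, 30% to 34% at 25, 11% to 15% at 30.
- *Control rate* (15 points, 110 per arm, 50/50): 46% at 50%, 48% at 60%, 50% at 70%, 44% at 80%.
- *Continuity correction* (15 points, 50/50): 40% to 44%.

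**7. Power of the interaction test.** Take 110 per arm, a 50/50 split and a variance of 0.25 per cell. The standard error of the difference between two arm differences is √(4 × 0.25/55) = 0.135.

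- Effects differing by 30 points: Φ(0.30/0.135 − 1.96) = 60%. Simulation on the logit scale at 242 patients, 0 v 30 points, gives about 72%.
- Effects differing by 15 points: Φ(0.15/0.135 − 1.96) = 20%.

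**The case against.** The strongest reply is that the protocol does not commit the error. Much of this stands.

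- **What the chi-square compares is not stated.** A reader might infer that arm is tested inside each subgroup, since that is the usual meaning of a sub-group analysis. The row does not say so. The independent variables that the table names are socio-demographic, behavioural and adherence factors, so a cross-tabulation of factor against adherence fits too. Under that reading the rates in the working do not apply, but the test still does not address item 3.
- **No identification rule is given.** A reader might infer that the plan will falsely identify a factor about half the time. That follows only if a factor is called a determinant when one level is significant and the other is not, and the protocol states no such rule.
- **Other methods are listed.** Logistic regression and structural equation modelling could both carry an interaction, and an analysis plan that is not shown may specify one. The chi-square is therefore the only method labelled for subgroups, not the only possible route. Still, neither entry names such a term, and the sub-group label is given to a test that cannot do the job.
- **Item 3 may be a loose restatement of objective 1.** This is possible. As worded, however, it concerns differences between the intervention and control groups, which objective 1 does not. If objective 1 is meant, the wording needs to change.
- **The rate does not rise steadily with the effect.** A reader might infer that the better the reminders work, the more often subgroup tests disagree. They disagree most near 15 to 20 points, and much less often at 25 and 30.
- **Endpoint and split.** The 15 points refer to adherence of at least 90%, not to the Good adherence category, which is cut at more than 95%. The subgroup splits are assumptions. For sex, the Background gives males as 90% but also females as 21% in 2011. Both are national figures, not figures for this clinic.

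**Conclusion.** The point holds as a mismatch between a stated aim and the method labelled for it. Item 3 asks about effect modification. The sub-group chi-square does not test that under either reading, and no arm-by-factor interaction is named.

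The size is conditional. About 45% to 58% false identification per two-level factor, against about 4% to 5% for an interaction test, rests on:

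- a common effect of 50% v 65% with adherence of at least 90%;
- 110 to 121 patients per arm;
- assumed splits from 50/50 to 90/10;
- uncorrected tests at 0.05;
- a rule of comparing within-subgroup p-values, which the protocol neither states nor rules out.

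The documents do not support saying that the trial will make this error, or that it could not fit an interaction with the methods it lists. The matter concerns an exploratory aim and leaves the primary comparison untouched. It is worth correcting because the correction is only a change of wording.

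**What to change.** Decide what item 3 means, then make aim and method agree.

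- **If effect modification is meant:** for item 3, replace the sub-group chi-square with an arm-by-factor interaction term in the logistic model already listed, with month-6 adherence as the outcome. Fix a few factors in advance, such as age and gender, which the protocol already names for the balance check. Report the arm effect in each subgroup with a 95% confidence interval beside the interaction p-value. State that no conclusion will be drawn from within-subgroup p-values.
- **If only predictors of adherence are meant:** reword item 3 to match objective 1, and state that the chi-square compares the factor with adherence.

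Either way the cost is wording: no further patients, data or software. The downside of the first option is modest power. At 50/50, an interaction of 30 points is detected with about 60% to 72% power and one of 15 points with about 20%. Fewer factors will be claimed, and a non-significant interaction must not be read as proof of an equal effect.
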